### Ethical considerations

Ethical approval for the study is obtained from the regional ethics review committee (CMO Arnhem-Nijmegen) and from the research ethics committees of all participating hospitals. All participating patients will sign an informed consent form.

## Discussion

This study attempts to settle the debate on the desirability of informing patients with cancer. To this end, the amount of information desired by patients with advanced cancer is investigated by offering information in a decision aid. Furthermore, the study will show whether it is possible to predict the amount of information desired, either by patient and disease-related factors, or by judgment of the medical oncologist. Concerns that the information may provoke patient anxiety are addressed by evaluating the effects of the decision aid using a randomized controlled design.

The study design has some limitations. Selection bias could be introduced when oncologists select patients who are more open to information or are in a better psychological state. When the data collection is completed, the role of selection bias can be investigated by comparing the resulting sample to other study samples, and comparing patient characteristics between physicians that included few versus many patients. Selective patient participation based on patients' information desire is addressed by informing eligible patients about the study in a general way, not mentioning the provision of (prognostic) information.

Patients have to fill in a baseline questionnaire that includes predictors for information desire and a baseline measurement for the effect of the information. Therefore, it is not feasible to include patients at the moment of the treatment choice; patients have to be included during first-line chemotherapy. This timing may positively affect the inclusion rate, since patients will be less distressed during first-line chemotherapy than at the moment of disease progression. On the other hand, due to the interval between the baseline questionnaire and the interview, the association between information desire and predictors may be weakened. In addition, the correlation between the effect measures at baseline (t1) and follow-up (t2 and t3) may be weakened.

Randomization is, for practical reasons, performed by using sealed envelopes. In some of the 11 participating hospitals, there will be little time between the diagnosis of disease progression and subsequent consultation with a nurse. Therefore, instant randomization will be required and envelopes are a very practical method to perform this. The use of envelopes leaves a possibility to subvert the randomization procedure. However, a plain attempt to allocate a patient out of sequence will be discovered because the envelopes are sequentially numbered and the allocation can be compared with the predetermined sequence. The oncologist could also decide not to randomize a patient, but this would not go unnoticed since all patients are registered on the trial before the moment of randomization, therefore we will be able to compare patients who were and were not randomized.

Blinding of the medical oncologists and the patients is not feasible in this type of research, because patients may want to discuss the information from the decision aid with their oncologist. However, patients are blinded to the intervention in that they are not aware of the exact content of the decision aid; they are only informed that a new method of information giving is investigated.

A major strength of this study is that, in contrast to many previous studies, we will actually deliver information on treatment options to patients at the point of decision making. The results of this study can be applied to improve the provision of information in daily clinical practice. Generalization to the target population is facilitated by the broad inclusion criteria that are used in this study and the use of the decision aid by various nurses in the 11 participating hospitals. Furthermore, the method used to assess patients' information desire very much resembles information giving in clinical practice, by actually providing information at the moment of the treatment choice.

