## Methods/Design

### Patients

In 11 hospitals in the Netherlands, all patients with advanced colorectal, breast, or ovarian cancer who have started treatment with first-line palliative chemotherapy and upon disease progression will be faced by the choice regarding second-line palliative chemotherapy will be included. Exclusion criteria are labile personality structure, as assessed by the physicians, a Karnofsky performance score lower than 60, and insufficient knowledge of the Dutch language. The study has been approved by the research ethics committees of all participating hospitals.

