### Randomization

Randomization will be performed to determine whether the patient will receive usual care (n = 70) or usual care plus the decision aid (n = 100). To accomplish this, a computer generated randomization list is prepared that is stratified by hospital, using a block size of 3. Each participating hospital will receive three sets of sealed envelopes, related to colorectal, breast, and ovarian cancer patients. When disease progression is diagnosed by the oncologist, a nurse will perform the randomization by opening the appropriate envelope.

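### A fixed block of 3 in hospital-by-tumour envelope sets could make up to about 4 in 10 allocations deducible, and the checks in the Discussion do not address this

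*Protocol article*

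**What the plan says.** Protocol article, Randomization: "a computer generated randomization list is prepared that is stratified by hospital, using a block size of 3". The same section continues: "Each participating hospital will receive three sets of sealed envelopes, related to colorectal, breast, and ovarian cancer patients". A hospital nurse opens the next envelope once progression is diagnosed. The planned arms are 100 (decision aid) and 70 (usual care). The split inside a block of 3 is not given.

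Protocol article, Discussion: "Blinding of the medical oncologists and the patients is not feasible in this type of research". On envelopes it says: "The use of envelopes leaves a possibility to subvert the randomization procedure". Two checks follow. Envelopes are numbered, so their use can be compared with the list. Patients are registered before randomization, so those randomized can be compared with those who were not. The second check answers this admission: "The oncologist could also decide not to randomize a patient".

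**The concern.** In an open trial, site staff can see past allocations. A very short block of one fixed size, run separately for each tumour type within each hospital, makes the next allocation deducible in part. If the split is 2:1, then once usual care has appeared in a block the rest of that block is decision aid, and the third place is always determined.

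The Background names physicians' worry that prognostic information provokes anxiety, and the Sample size section makes HADS anxiety the main outcome for question 3. The people who could foresee the arm therefore have a plausible motive linked to that outcome. If distressed patients were kept out of foreseeable decision-aid places, the decision-aid group would look calmer and the comparison would lean towards no harm. Questions 1a, 1b and 2 do not rest on the comparison between arms.

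**Working it through.** **The plan's own figures.** The article gives no figure for predictability. Its relevant figures are the arm sizes, 100:70, a ratio of 1.43.

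**Inputs.** Block size 3 and three envelope sets per hospital (Randomization); 11 hospitals (Patients), hence 11 × 3 = 33 sets; 170 patients, hence 170/33 = 5.2 per set on average.

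**Assumption.** The split is 2:1 (A = decision aid, B = usual care). It is the only fixed split of 3 that contains both arms and favours the decision aid. It does not reproduce the planned arms: 170 × 2/3 = 113 and 170 × 1/3 = 57.

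**Complete blocks at 2:1.** The sequences AAB, ABA and BAA are equally likely.
- Place 1 is never certain.
- Place 2 is certain only after B, with probability 1/3.
- Place 3 is always certain.
- Share certain = (0 + 1/3 + 1)/3 = 4/9 = 44%.

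In general, a block with a and b places has a/(b+1) + b/(a+1) certain places on average. For 2:1 this is 2/2 + 1/3 = 1.333, and 1.333/3 = 44%.

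**Incomplete last blocks at 2:1.** Spreading 170 patients at random over 33 equal sets and counting certain places gives 38%. Unevenly sized sets (assumed weights) also give 38%.

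**Other reading of the split.** Suppose 2:1 and 1:2 blocks were mixed at random to reach 10:7. The share q of 2:1 blocks solves 1 + q = 3 × 10/17, so q = 0.765. Only the third place after AA or BB is then certain. Its probability is q/3 + (1 − q)/3 = 1/3, so the share is (1/3)/3 = 11%. The article describes no such mix.

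**Alternative blocks at 3:2.**

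| Blocks | Complete blocks | 33 sets, incomplete last blocks |
|---|---|---|
| 3 (2:1) | 44% | 38% |
| 5 (3:2) | (3/3 + 2/4)/5 = 30% | about 21% |
| 10 (6:4) | (6/5 + 4/7)/10 = 18% | about 3% |
| 5 and 10 in random order, each size known | – | about 11% |

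If the sizes are not known, the last figure is lower still. Expected arms at 3:2 are 170 × 0.6 = 102 and 68. The simulated standard deviation of the decision-aid count is about 2.2 for blocks of 3 and about 3.7 for random 5 and 10.

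**The two checks against the routes to bias.**

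| Route | Numbered envelopes | Randomized versus not randomized |
|---|---|---|
| Opening out of sequence | detected | – |
| Registered patient never randomized | – | detected afterwards |
| Deducing the next arm | not addressed | not addressed |
| Delaying or reordering patients, envelopes used in order | not seen | not seen |

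**The case against.** The strongest reply has four parts.

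- **The 38% to 44% is a ceiling.** It depends on an unstated split that does not give 100:70. It also requires staff to know or infer the block size and to track a list of about five patients, possibly across several nurses. Whether sites were told the block size is a detail an article may leave to the full protocol, so silence on it is no fault. This stands: the figures describe what could be deduced, not what staff know.
- **Enrolment cannot easily be steered.** Consent, registration and the baseline questionnaire, including HADS, come before randomization. A patient who is withheld leaves a trace. This stands.
- **There is little room for timing.** Progression triggers randomization, the Discussion says some hospitals have little time before the nurse consultation, and reordering needs another patient with the same tumour at the same hospital. This stands in part; it narrows the route without closing it.
- **The analysis adjusts for baseline.** The analysis of covariance deals in part with selection on anxiety measured at t1. It cannot deal with distress that arises between t1 and progression, and the Discussion itself notes that this interval may weaken the correlation with follow-up.

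A reader might infer that staff will know 4 in 10 allocations and that randomization no longer protects the anxiety result. The documents do not support that. They do not show that staff hold the needed knowledge, and the safeguards above limit what could be done with it. Nor is the Discussion's sentence on envelopes an error: it is a disclosed limitation with a practical reason. What it leaves out is predictability.

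**Conclusion.** The point holds as a conditional design weakness that should be mended. The article fixes a single block size of 3 within 33 small sets in an unblinded trial. Assuming 2:1, 38% to 44% of allocations could be deduced with certainty by staff who know or infer the block size and follow earlier allocations; under a random mix of 2:1 and 1:2 blocks the share is 11%. The stated checks reveal out-of-sequence opening and failure to randomize, but only afterwards. They do not prevent deduction of the next arm and do not reveal delay or reordering.

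The exposure is confined to the between-arm comparison in question 3, through selection on distress arising after t1. The documents give no basis for expressing that bias in HADS points, and they do not show that it will occur. Separately, a fixed 2:1 block of 3 (about 113:57) and the planned 100:70 need to be reconciled.

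**What to change.** Replace the fixed block of 3 with randomly ordered block sizes that are not disclosed to the hospitals, for example 5 and 10 at 3:2, and keep the sizes out of documents held at the sites. The change of ratio is deliberate: 3:2 gives about 102:68, close to the planned arms. Have the nurse write patient ID, date and time on each sealed envelope before opening it, so that delay and reordering leave a record. State the within-block ratio in the Randomization section.

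Envelopes stay, so randomization remains instant. The cost is a new list and new envelopes, and slightly looser balance (standard deviation of the decision-aid count about 3.7 instead of about 2.2).
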